### Training approach 2 and data collection: Traditional group training of participants – Group 2 or control group

The traditional training approach will consist of 8 days of lectures with practice sessions on simulators, off-site the participants’ workplace, usually in a hotel. Oral consent will be obtained, the participants will take pre-training assessments consisting of MCQs and OSCEs through use of manikins, to assess their baseline knowledge and skills respectively. The assessments will test their knowledge and skills on conduct of normal delivery, AMTSL, neonatal resuscitation, case management of PEE and management of PPH (e.g. manual removal of placenta, internal bimanual uterine compression and compression of the abdominal aorta). This group then receives lectures and practice sessions on conduct of normal delivery, AMTSL, neonatal resuscitation, case management of PEE and management of PPH. The Nigerian BEMONC package and clinical observation checklists are used during the training sessions. The group-based training approach will include training sessions consisting of 8 days of lectures and fewer practice sessions using manikins (MamaNatalie/NeoNatalie) offsite and not at the trainees’ place of work. Table 1 outlines the basic similarities and difference between the two groups. At the end of the eight-day training, the participants will undergo an immediate post-training assessment which includes MCQs and OSCEs. As described among arm 1, the questions answered correctly and procedure done competently will be scored out of a total of 100%, assessments results will be compared and trainees satisfaction survey will be conducted.

**Table 1 Tab1:** Comparison of the Simulation-based LDHF and Group-based study arms

Parameters of the interventions received	Simulation-based LDHF Arm	Group-based Arm
Training covers BEMONC	Yes	Yes
Training is onsite	Yes	No
More frequent practise sessions using manikins during training	Yes	No
Post-training Practise Sessions with manikin in facility	Yes	No
Presence of PPCs	Yes	No
Use of mobile phone for post-training support	Yes	No
All courses divided into two phases which are 1 month apart	Yes	No

### Cost effectiveness analysis

As part of LDHF and TRAD evaluation activities, we will prospectively monitor the costs of both approaches across two perspectives: (1) incremental program costs, and (2) costs to providers/ health system. Incremental program costs include costs incurred by Jhpiego in the implementation of LDHF and/or TRAD training across three distinct phases: development, start-up and ongoing implementation support. Costs will be collected according to an ingredients approach and differentiated according to capital (costs with a life expectancy of greater than 1 year) and recurrent costs. The former will be annualized drawing from standardized WHO-CHOICE life expectancy estimates and discounted at 3%. Costs incurred by providers / health system primarily focus on the opportunity costs of in-service training to providers and the health system. These will be captured through questions imbedded into knowledge surveys. Efforts to determine the value for money of LDHF vs. TRAD training will draw from data on the incremental costs and effects of program activities. Incremental costs will be collected throughout the 1-year analytic time horizon of the program and presented in 2018 United States Dollars. Incremental effects will be drawn from data mentioned above and utilize composite scores of knowledge and competency.

### Data analysis

#### Primary outcome

Clinical competency level in BEmONC skills of service providers at 3 months post-training.

#### Secondary outcomes

Retention in clinical competency level in BEmONC skills as assessed through OSCEs and MCQ scores at 12 months post-training.Service provider satisfaction with a simulation-based LDHF/m-Mentoring and group-based training approaches.Direct cost and cost-effectiveness of LDHF/m-Mentoring and group-based training approaches.

#### Descriptive analysis

Absolute numbers and simple percentages will be used to describe categorical variables. Measures of central tendency (mean and median) as well as dispersion (range and standard deviation) will also be determined. The unit of analysis will be the service providers. First, we will check the balance between the two treatment arms in terms of potential confounding factors, such as provider- (age, experience) or facility-(location, level of healthcare delivery, ownership)-level characteristics. In addition, pre-test scores is compared between the groups, overall and stratified by location and level of healthcare delivery. Percentage of those achieving the required competency level (≥80% post-training scores in each of MCQ and OSCE) for both groups 1 and 2 is calculated. This will be done for pre-training and subsequent post-training follow-up assessments. Composite scores will be computed for selected variables to determine areas where service providers have good skills as against areas where their skills are poor.

#### Inferential analysis

Generalized linear model with robust facility-level variance will be used to test the differences between arms in MCQ scores, OSCE scores and satisfaction outcomes at 3 months using a group indicator as the main predictor in the model. Additionally, we will adjust for provider- and facility-level characteristics that show imbalance between arms at baseline and can be strongly correlated with the outcome scores. A *p*-value < 0.05 will be considered statistically significant. The number of short messages sent is assessed for trend of the reply and correct answers. The frequency and trend of mentorship call will also be assessed. The model described for the primary outcome is used to look at the outcomes at other time points. In addition, we will develop a longitudinal model that assess the change in scores (or competency level) over time post-training. This model is appropriate, since it accounts for correlation within a provider over time as well as within-facility correlation of scores. Generalized linear population-average model estimated using generalized estimating equations (GEE) with working exchangeable correlation structure is used. The amount of missing data is assessed for each variable and overall for the sample. If more than 5% of data are missing, multiple imputation procedure is used assuming missing at random. Composite scores is computed for the satisfaction survey. A Decision Tree will be used to compare incremental costs and incremental effects by provider across the two study arms. One-way, multi-way and probabilistic sensitivity analyses are conducted to assess uncertainty.

Qualitative data analysis: Notes and transcripts will be entered into Atlas-ti version 8 software. Content analysis of the discussions will be undertaken to generate themes of interest along which the analysis will be done. Analysis will be by themes across location and classifications of the groups.

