### Sample size

We will calculate the average number of providers who will be included from each of the 60 facilities (or 30 facilities in each arm) using a test of two proportions for a binary indicator of a present competency score. Competency will be assumed at a score of 80% or higher score on both the knowledge and skills assessments. We assumed that the proportion of competent providers will be 50% in the control group. The goal is to have at least 80% power to reject a null hypothesis that the proportions are equal across the two arms against the alternative hypothesis of a minimum effect size of 20 percentage point difference in proportions of competent providers. The test of hypothesis will be performed at 0.05 level of significance. Sample size was calculated using PASS statistical software [14]. Since some facility-level factors that are shared by the providers working in the same facility can influence the competency level, we will assume 0.05 within facility correlation of competency levels across providers in a given health facility**.** Assuming that an average of four (04) service providers sampled per health facility, a total of 240 providers across the two groups will be needed so that there will be at least 80% power to detect a 20 percentage point difference in competence level between the two arms (assessment at 3 months) at 0.05 level of statistical significance. The final sample size will be 300 or 150 providers per study arm to account for potential 20% drop-out at the time of post-training assessment. The participants for each facility will include the maternity unit head wherever possible and two others; to ensure the other team members receive the necessary support they need to practice the competencies. Study participants will be administered a single survey comprised of modules on characteristics, knowledge, and costs incurred in addition to a competency assessment prior to training and at three time points following training (end of training day, 3, 12 months post-training).

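### The planned analysis allows only for within-facility correlation, but TRAD courses almost certainly pool facilities; if outcomes differ between courses, type I error can exceed 5%

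*Protocol article*

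**What the plan says.** Facilities are the randomized units (Randomization). The Sample size section plans for "an average of four (04) service providers sampled per health facility", a within-facility correlation of 0.05 and no other level of clustering. Inferential analysis commits the 3-month comparison to the following: "Generalized linear model with robust facility-level variance will be used to test the differences between arms". It defends the longitudinal GEE on the ground that "it accounts for correlation within a provider over time as well as within-facility correlation of scores". Neither model has a level for training course or trainer.

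Delivery differs by arm. LDHF training takes place at the health facility for its whole team, so training group and facility coincide. For TRAD the article says: "The group-based training approach will include training sessions consisting of 8 days of lectures and fewer practice sessions". These courses are held away from the workplace, usually in a hotel. Background describes this style of training as drawing only a few staff from each site at a time. The article does not give the number of TRAD courses, their size, or how trainers are allocated to them.

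**The concern.** A facility-clustered variance is valid when facilities within an arm are independent. TRAD facilities whose staff attend the same course share trainers, venue and week, and can do well or badly together. The facility-level estimator counts them as separate pieces of evidence. One strong or weak trainer team could then move several TRAD facilities at once and look like an effect of the training approach.

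The trial is meant to advise the Ministry of Health on which approach to invest in. A p-value or interval that is too optimistic would feed directly into that advice.

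**Working it through.** **Inputs from the article (Sample size):** 30 facilities per arm; 4 evaluable providers per facility; facility ICC 0.05; 50% versus 70% competent; alpha 0.05 (two-sided assumed); power at least 80%; 20% dropout. **Assumed, because not given:** S TRAD courses of equal size, and session ICC ρ. Outcome variance is set to 1 in each arm.

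**1. The plan's own figure.** Per arm, n = [1.96√(2×0.6×0.4) + 0.8416√(0.25+0.21)]² / 0.2² = (1.358+0.571)²/0.04 = 93. With continuity correction, 93/4 × [1+√(1+4/(93×0.2))]² gives 103. The design effect is 1+(4−1)×0.05 = 1.15. Then 103×1.15 gives 119 per arm, 238 in total, which agrees with 30×4×2 = 240; and 240/0.8 = 300. Power at 240 is 80.7% with the correction and 84.4% without. The sample size is therefore sound for facility clustering alone.

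**2. True versus estimated variance of the arm difference.**
- LDHF mean: (0.05+0.95/4)/30 = 0.2875/30 = 0.009583.
- TRAD mean, true: [0.05+(0.95−ρ)/4]/30 + ρ/S.
- TRAD mean, as the facility-level estimator sees it on average, with k = 30/S facilities per course: [0.05+(0.95−ρ)/4 + ρ(1−(k−1)/29)]/30.

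Example with S = 6, ρ = 0.05. True: 0.275/30 + 0.05/6 = 0.017500; adding LDHF gives 0.027083. Estimated: (0.275+0.05×25/29)/30 = 0.010603; adding LDHF gives 0.02019. SE ratio = √(0.027083/0.02019) = 1.158. Type I error = 2Φ(−1.96/1.158) = 9.1%.

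Type I error of the facility-level test:

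| Session ICC | 10 courses | 6 courses | 5 courses |
|---|---|---|---|
| 0 | 5.0% | 5.0% | 5.0% |
| 0.01 | 5.4% | 5.8% | 6.0% |
| 0.05 | 7.0% | 9.1% | 10.1% |
| 0.10 | 8.8% | 12.7% | 14.6% |

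With 30 courses (one facility each) it is 5.0% throughout. Outside the table, it is 5.2% for 15 courses at ICC 0.01 and about 22% for 3 courses at ICC 0.10. A simulation with a binary outcome (6,000 runs, t with 58 df) agrees: 5.2-6.2%, 6.4-9.4% and 9.1-15.0% at ICC 0.01, 0.05 and 0.10 for 5 to 10 courses.

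**3. Session-aware test.** Clustering TRAD on course and LDHF on facility, with Satterthwaite degrees of freedom, gave simulated type I error of about 5.0-5.5% on facility means and 4.5-5.9% in the binary simulation.

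**4. Power at 50% versus 70%, 240 evaluable.** With no session effect, simulated power is 84% for the facility test. For the session-aware test it is 82.5%, 80% and 77.6% with 10, 6 and 5 courses.

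With a session effect, the TRAD design effect is 1.15+(120/S−1)ρ. At S = 6, ρ = 0.05 it is 1.15+19×0.05 = 2.10. Then SE = √(0.25×2.10/120 + 0.21×1.15/120) = 0.0799, and power = Φ(0.2/0.0799−1.96) = 70.6%. At S = 10 it is 76.5%. The same formula without a session effect gives 85.4%.

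That formula treats the variance as known. With the small-sample reference, at S = 6, df = (0.0020125+0.004375)²/(0.0020125²/29+0.004375²/5) = 10.3, the critical value is 2.22, and noncentral-t power is about 62%. At S = 10 the same steps give df 20.1 and about 72%.

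**The case against.** **Pooling is inferred.** The article nowhere says that facilities share a course, and a reader might take it as stated. However, unpooled delivery would need 30 separate 8-day off-site courses of about five people each. The inference is strong but remains an inference.

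**No session ICC is given.** A reader might conclude that the planned test does exceed 5%. The documents do not support that: at ICC 0.01 with 10 courses the excess is negligible. The conditional wording is needed.

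**With no training effect at all there would be no course effect.** This has little force. Both arms are actively trained, and the hypothesis set out under Sample size is equality between arms: "The goal is to have at least 80% power to reject a null hypothesis that the proportions are equal across the two arms". Equal arm means are compatible with better and worse TRAD courses.

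**Randomization is stratified and the model does not name the strata.** This could push the standard error upward and offset part of the inflation, by an unknown amount. It does not remove course effects, which arise after randomization.

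**LDHF may have its own shared level.** Trainers and master mentors may serve several facilities; the number is not stated. This stands: it should not be assumed that facility clustering is fully right in LDHF.

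**Colleagues from one facility may attend different courses.** Course and facility would then be crossed, and replacing one by the other would lose the planned within-facility correlation. This also stands, and it shapes the fix.

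**A condensed article may leave the detail to a fuller plan.** That is fair for the recording of course membership. But the article itself chooses the clustering level and calls the longitudinal model appropriate on that ground. Facility clustering is the conventional minimum here. Whether to generalise beyond the courses delivered is partly a choice of estimand, yet the stated purpose of advising on a training approach points to generalising.

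**Conclusion.** The point holds conditionally. The clustering level does not match how TRAD is almost certainly delivered, and the direction of the error is known: if session ICC is above zero and courses pool facilities, the facility-level standard error is too small.

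At a session ICC equal to the plan's own facility value of 0.05, type I error would be about 7-10% for 5 to 10 courses. It would be about 5-6% at 0.01 and 9-15% at 0.10. There is no inflation if the session ICC is zero or each course holds one facility. These figures assume equal courses, facilities nested in courses, four evaluable providers per facility and no shared trainer effect in LDHF. They are derived on facility means, so they apply to the MCQ, OSCE and satisfaction scores as well as, approximately, to the competent/not competent endpoint.

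The stated 240 and 300 reproduce and are not in error on their own assumptions; they simply contain no allowance for courses.

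**What to change.** - State the number of TRAD courses and the facilities per course. Record the course and trainer for every TRAD participant, and the trainer and mentor for LDHF. Membership may be hard to reconstruct later.
- Pre-specify one session-aware analysis of the 3-month comparison: a partially nested model that keeps the facility effect, adds a course effect in TRAD only, and uses a small-sample reference. If facilities are nested in courses, a Welch-type test on course summaries in TRAD and facility summaries in LDHF is a simple alternative, and it suits the binary endpoint.
- Report it beside the facility-robust result with the estimated session ICC. Qualify any claim of a difference that does not hold there. Do not require significance in both tests: the session-aware test already holds about 5%, and a double requirement only costs further power.
- Recheck power over a range of session ICC.

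Cost: a few data fields and one model, with fewer degrees of freedom. Power is about 78-82% instead of 84% if there is no session effect. At session ICC 0.05 with 6 to 10 courses it is about 71-77% on the large-sample formula and about 62-72% with the small-sample reference. Most of that loss is the design's true precision, which the facility-level analysis would hide; the rest is the price of estimating between-course variation from few courses.

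### The trial is powered on a binary endpoint (at least 80% on both MCQ and OSCE at 3 months), but the 3-month primary-outcome model lists separate scores, so the powered test is not stated in the analysis section

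*Protocol article*

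**What the plan says.** Four sections of the protocol article bear on this point.

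- **Sample size.** The calculation is made "using a test of two proportions for a binary indicator of a present competency score". The indicator is defined on two components: "Competency will be assumed at a score of 80% or higher score on both the knowledge and skills assessments". The planning values are "We assumed that the proportion of competent providers will be 50% in the control group" and "a minimum effect size of 20 percentage point difference in proportions of competent providers", assessed at 3 months, with at least 80% power at the 0.05 level. This section also says that the hypothesis of equal proportions will be tested.
- **Primary outcome.** It reads: "Clinical competency level in BEmONC skills of service providers at 3 months post-training". It does not say whether this is a yes/no indicator or a score.
- **Descriptive analysis.** The "Percentage of those achieving the required competency level", with the threshold applied to each of MCQ and OSCE, is calculated for each arm before training and at each follow-up. No between-arm test is attached.
- **Inferential analysis.** A generalized linear model with robust facility-level variance is used to "test the differences between arms in MCQ scores, OSCE scores and satisfaction outcomes at 3 months", with p < 0.05 as the criterion. The section then says "The model described for the primary outcome is used to look at the outcomes at other time points". Competency level appears in this section only in brackets, as an alternative to scores in the longitudinal GEE model of change after training.

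Satisfaction is listed under Secondary outcomes.

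**The concern.** The endpoint that determines the number of providers and the outcomes in the model that carries the primary label are not the same. One is a single yes/no indicator that needs both tests passed. The others are two separate scores, with a secondary outcome in the same sentence.

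The difference can change the conclusion. Mean scores can differ between arms without more providers passing 80% on both tests, for instance if the gain is among providers already above the threshold or still well below it. The reverse can also happen. If MCQ scores improve and OSCE scores do not, the article does not determine whether the primary hypothesis succeeded. The result is meant to advise the Ministry of Health on how to train birth attendants, so the test behind the main claim should be fixed in one place and match the one that was powered.

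**Working it through.** **1. Which endpoint does the sample size belong to?**

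Inputs from Sample size: control proportion 0.50; difference 0.20, so 0.70 in the LDHF arm; power 0.80; alpha 0.05; within-facility correlation 0.05; 4 providers per facility; 30 facilities per arm; 20% drop-out. Sidedness and the exact formula are not stated; the two-sided, continuity-corrected form below is the one that reproduces the article's figure.

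- Uncorrected n per arm = [1.960 × √(2 × 0.6 × 0.4) + 0.842 × √(0.5 × 0.5 + 0.7 × 0.3)]² / 0.20² = 93.
- With continuity correction, n × [1 + √(1 + 4 / (n × 0.20))]² / 4 = 103.
- Design effect = 1 + (4 − 1) × 0.05 = 1.15.
- 103 × 1.15 = 118.45, so 119 per arm or 238 in total. In whole facilities, 118.45 / 4 rounds up to 30 per arm, and 30 × 4 × 2 = 240.
- Drop-out: 240 / (1 − 0.20) = 300.

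Both stated figures, 240 and 300, reproduce. Without the continuity correction the total is 214. One-sided totals are 172 (uncorrected) and 192 (corrected). The sample size is thus tied to the two-proportion test of the binary indicator. The article gives no mean difference or standard deviation for MCQ or OSCE scores, so it makes no power statement for them.

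**2. Which endpoint does the 3-month model test?**

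| Section | Form of the outcome | 3-month between-arm test stated there? |
|---|---|---|
| Sample size | Binary, both components at least 80% | Hypothesis of equal proportions stated; no model |
| Primary outcome | Competency level, form not given | No |
| Descriptive analysis | Binary percentage by arm | No, calculated only |
| Inferential analysis, 3-month model | MCQ scores, OSCE scores, satisfaction | Yes |
| Inferential analysis, longitudinal model | Scores or competency level | No, change over time |

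The only row with an explicit 3-month between-arm model does not contain the powered endpoint.

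**3. What does this do to the primary type I error?**

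It depends on a success rule that the article does not give. For MCQ and OSCE each tested at 0.05:

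- Either one suffices, independent tests: 1 − 0.95² = 0.0975.
- Either one suffices, correlated test statistics (assumed correlations, since the article gives none; simulated): about 0.091 at 0.5, 0.084 at 0.7, 0.070 at 0.9.
- Both required: at most 0.05.

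**4. What does testing the binary indicator cost?**

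With 240 evaluable providers the effective number per arm is 120 / 1.15 = 104.3. Power is Φ[(0.20 × √104.3 − 1.960 × √0.48) / √0.46] = 0.84 (two-sided, uncorrected normal approximation). This is a recomputed value; the article claims only at least 80%. One test at 0.05 needs no further adjustment.

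**The case against.** The strongest reply is that the mismatch is one of wording. Sample size says that equality of proportions will be tested. A generalized linear model can take a binary outcome, and the longitudinal model allows competency level. The remark about the model for the primary outcome can be read as referring to the type of model, reused at other time points. A condensed article with no analysis plan shown may also leave multiplicity rules to that plan.

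Much of this stands, and it rules out three stronger readings:

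- A reader might infer that the powered hypothesis is never tested. The documents do not support that, given the statement in Sample size and the option in the longitudinal model. What is missing is the explicit 3-month test in the section that sets out the tests.
- A reader might count three tests and quote 1 − 0.95³ = 14.3% as the primary error rate. Satisfaction is a secondary outcome, and nothing says that a significant satisfaction result counts as success.
- A reader might take type I error inflation, or a loss of power, as established. Inflation arises only under an either-suffices rule, and the definition of competency, which requires both components, points the other way. Nor need score analyses be weaker. As an illustration, assume one normally distributed score cut at the threshold: 50% to 70% is then a shift of 0.52 SD, and 120 per arm with design effect 1.15 gives power of about 97%.

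The word skills in the primary outcome is also not a clear contradiction, because Secondary outcomes uses the same phrase and says it is assessed through both OSCEs and MCQs.

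The reply does not remove the discrepancy itself. The absence of a multiplicity rule is not the complaint. The article does state a 3-month model and does list its outcomes, and that list omits the endpoint on which the trial was sized.

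**Conclusion.** The point holds as a mismatch between Sample size and Inferential analysis. Followed as written, the analysis section gives no 3-month between-arm test of the powered endpoint, the statement of at least 80% power does not describe the tests that are listed, and no single listed test decides the primary question.

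The consequence for type I error is conditional: up to 9.75% if either score alone were accepted as success and the tests were independent, about 7% to 9% under assumed correlations of 0.9 to 0.5, and no inflation if both are required. The sample size is not at fault. It reproduces under a two-sided, continuity-corrected calculation, which is an inference from the match and is not stated in the article.

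**What to change.** In Inferential analysis, name one primary test: the proportion of providers scoring at least 80% on both MCQ and OSCE at 3 months, compared between arms in the generalized linear model for a binary outcome, with robust facility-level variance, at two-sided 0.05. Label the separate MCQ and OSCE scores and satisfaction as secondary or supportive. Give the same definition under Primary outcome, so that it agrees with Sample size and Inferential analysis. The choice of effect measure and any formal ordering of the secondary tests can be left to the authors.

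The cost is a change of wording. The 3-month assessments are already planned and the sample size stays at 240 evaluable and 300 recruited. The one small downside is that a difference on a single score can no longer be presented as the primary result.
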